### Evaluation of mediation

We will investigate the mediation process of different aspects of caregiver wellbeing and, through that, illuminate key basic knowledge about generalization of acquired skills in parenting through the CSI intervention. Some of the pathways of interest are illustrated in Fig. 4. If the efficacy analysis shows significant between-group differences in the mediators (caregiver stress (Caregiver Stress Scale), caregiver distress (K10), caregiver psychosocial wellbeing (WEMWBS), stress management), then we will use parametric regression models to:
Test for mediation of the intervention on Parenting through caregiver stress (Caregiver Stress Scale)Test for mediation of the intervention on Parenting through caregiver distress (K10)Test for mediation of the intervention on Parenting through caregiver psychosocial wellbeing (WEMWBS)Test for mediation of the intervention on Parenting through stress management (Stress Management Scale).

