Parenting programs focused on knowledge and skills development *have* shown small to moderate effects on parenting outcomes in several studies, suggesting that addressing caregiver wellbeing directly may not be essential to achieving some benefit [21]. It remains to be seen whether the modest effects attained thus far might be strengthened by making stress reduction and improved caregiver wellbeing primary targets rather than collateral outcomes of parenting interventions.

The Caregiver Support Intervention (CSI) has a dual focus on strengthening caregiver psychosocial wellbeing and increasing knowledge and skill regarding parenting under conditions of adversity. The guiding hypothesis underlying the CSI is that under conditions of lowered stress and increased wellbeing, caregivers will become better able to make more effective use of both pre-existing and newly acquired parenting knowledge and skills. Figure 1 depicts the model that guided the development of the CSI. The dotted lines show the relationship between war exposure and daily stressors with children’s wellbeing. The solid lines illustrate the key model underlying the CSI, in which war exposure and daily stressors adversely affect caregiver wellbeing, which in turn negatively affects parenting, ultimately impacting children’s wellbeing.

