### Baseline, post-intervention, and follow-up assessments

Questionnaire data will be gathered at three time points: baseline, post-intervention, and 3-month follow-up. Because the study will be implemented in two waves, there will be a total of six assessments, three in each wave. This is depicted in the SPIRIT figure chart in Fig. 2.

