#### Data analysis

The statistical analyses will be carried out by the trial statistician, who will remain blind to the group randomization until the main analyses are complete. The analyses outlined in this strategy will be primarily based on an intention to treat (ITT); a per protocol (PP) analysis will be the secondary analysis. The PP analysis will include participants who complete the CSI, with completion defined as attending at least seven of the nine sessions, and will exclude any participant who attended fewer than seven sessions. We have powered the study (see the “Sample size” section) as a superiority study at 10 weeks. The first stage of analyses will be a descriptive model of the data to assess completeness of data and the integrity of the data collection system. Participants and area characteristics and demographics will be summarized at baseline. Clinical characteristics that have been measured repeatedly will be summarized at baseline and at the post-randomization follow-up assessments. In addition, patterns of missing data will be described.

The primary outcome (total score of parenting scale) will be analyzed using linear mixed models to model the mean difference in the total score of parenting scale 10 weeks post-randomization. The linear mixed models will be adjusted for baseline total score of parenting scale and stratification. A two-level hierarchical model will be employed to improve power and take into account clustering of the parents at the family level.

These models utilize maximum likelihood estimation and thus allow for missing outcome data under the missing at random (MAR) assumption. Associations between post-randomization variables and missingness will be dealt with by multiple imputation (MI), again under the MAR assumption. Departures from this assumption will be assessed with a sensitivity analysis.

Secondary outcomes, including parental warmth and responsiveness, harsh parenting, parenting knowledge, caregiver psychosocial wellbeing, and child psychosocial wellbeing will be assessed with a similar methodology used for the primary outcomes, using generalized linear mixed models depending on the type of outcome (normal, ordinal).

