**Fig. 4 Fig4:**
[figure not shown]
Putative mediation of impact of CSI on parenting by caregiver stress, caregiver distress, caregiver psychosocial wellbeing, and stress management. Solid lines represent mediational pathways to be tested

Since all the measures are continuous, the indirect effects will be calculated by multiplying relevant pathways and bootstrapping will be used to produce valid standard errors for the indirect effects. All analyses will adjust for baseline measures of the mediators (Caregiver Stress Scale, caregiver distress (K10), stress management, outcome (Parenting scale) and putative measured confounders (e.g., socioeconomic status).

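### Mediation is modelled only if the mediator differences are significant, so a stated objective would be reported selectively, with indirect effects biased upward when mediator effects are small

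*Protocol article*

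**What the plan says.** The Specific objectives list, as a secondary aim, assessing how four aspects of caregiver wellbeing mediate the effect of the CSI on parenting. The Background gives this its weight: "The guiding hypothesis underlying the CSI is that under conditions of lowered stress and increased wellbeing", caregivers will make better use of their parenting skills.

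The section Evaluation of mediation makes the analysis conditional: "If the efficacy analysis shows significant between-group differences in the mediators", with the four mediators named in brackets, "then we will use parametric regression models to" test mediation through each of them. The text under Fig. 4 says that indirect effects are products of paths and that "bootstrapping will be used to produce valid standard errors for the indirect effects". It also plans adjustment for baseline mediators, baseline Parenting score and measured confounders.

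For the primary outcome, the Data analysis section fixes the time point ("We have powered the study (see the “Sample size” section) as a superiority study at 10 weeks") and the handling of families ("A two-level hierarchical model will be employed to improve power and take into account clustering of the parents at the family level"). The mediation text repeats neither. Three assessments are planned: "Questionnaire data will be gathered at three time points: baseline, post-intervention, and 3-month follow-up".

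**The concern.** An indirect effect is the arm-to-mediator path multiplied by the mediator-to-outcome path. Estimating it only when the first factor is significant has two consequences.

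- **Missing estimates.** A mediator with a real effect that lands just short of significance yields no indirect effect and no interval. The reader cannot tell a negligible indirect effect from one the trial could not resolve.
- **Upward bias.** Where the estimate is reported, its first factor has passed a threshold, so on average it overstates the truth. The bias is large when power for that mediator is low and vanishes when power is high.

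The condition is also undefined across the four mediators. The readings each, any and all lead to very different chances that a given estimate appears. The analysis that triggers the condition is not clearly identified either. Of the four mediators, only caregiver psychosocial wellbeing is named among the outcomes in Data analysis, although that list is not exhaustive.

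At stake is how far the trial can speak to the mechanism it was built to test. The primary comparison is not involved.

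**Working it through.** The document gives no power, effect size or ICC for any mediator, so there is no stated figure to reproduce. The check asks how much the condition could matter in a trial of this size.

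**Inputs**
- Analysed caregivers: 480 less 20% attrition = 384 (Statistical power and sample size).
- ICC 0.15 and baseline-to-outcome correlation 0.6 (same section). Both are for the parenting score. Carrying them over to the mediators, and treating 0.15 as a family-level ICC with two caregivers per family, are assumptions.
- Arm-to-mediator effect a: not stated; 0.2 and 0.3 SD are used as a range.

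**Standard error of the arm-to-mediator path, in SD units**

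SE = √[(4/384) × (1 + (2 − 1) × 0.15) × (1 − 0.6²)] = √[0.01042 × 1.15 × 0.64] = 0.088.

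Without any gain from baseline adjustment: √[0.01042 × 1.15] = 0.109.

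**Power and selection**

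With d = a/SE, and ignoring the negligible opposite tail, power is Φ(d − 1.96). The mean of the estimate given significance, relative to the truth, is 1 + φ(d − 1.96) / [d × Φ(d − 1.96)].

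| a | Baseline adjustment | d | Chance of an estimate | Chance of none | Inflation of the path |
|---|---|---|---|---|---|
| 0.2 SD | correlation 0.6 | 2.28 | 63% | 37% | 1.26 |
| 0.3 SD | correlation 0.6 | 3.43 | 93% | 7% | 1.04 |
| 0.2 SD | no gain | 1.83 | 45% | 55% | 1.48 |
| 0.3 SD | no gain | 2.74 | 78% | 22% | 1.14 |

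**Does the bias reach the indirect effect?**

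A simulation of the product of paths used 192 families of two, a mediator-to-outcome slope of 0.4, no baseline covariates, ICC 0.15, family-level resampling and 400 runs. Estimates that passed the condition averaged:
- a = 0.2: 0.122 against a true 0.080 (ratio 1.53)
- a = 0.3: 0.136 against 0.120 (ratio 1.13)
- a = 0.4: 0.167 against 0.160 (ratio 1.04)

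The first two agree with the no-gain rows above, so the bias passes through almost in full.

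**False positives**

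With a = 0 in the same simulation, the indirect effect was declared non-zero in 4.5% of runs with the condition and 5.5% without it. The condition does not raise type I error.

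**Each, any or all**

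Take an assumed 80% power per mediator. An all-four rule is met in 0.8⁴ = 41% of trials if the mediators are independent, and in about 56% if they correlate at 0.5. An any-of-four rule is met in over 96% in either case. The wording alone decides whether the objective is usually or rarely reported.

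**The case against.** A significant arm-to-mediator path is the first step of a joint-significance test of mediation, so the condition is a recognised way to proceed. It costs little power: in the simulation at 0.3 SD, 80.0% with the condition against 81.8% without. The arms must be compared on each mediator to apply it, so the first link of the hypothesis is examined in any case. All of this stands. It defends the condition as a test. It does not defend leaving out the estimate and its interval, or the upward selection of those that are shown.

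Three stronger readings are tempting, and the document does not support them.

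- **That inflation is 1.4- to 1.8-fold.** This needs 30% to 50% power. Under the adjusted inputs above, 30% power corresponds to an effect near 0.13 SD. The pilot's medium or larger changes are within-group and cannot be read as between-group effects, but they do not point to so small a value.
- **That the bootstrap ignores families and its standard errors are invalid.** No resampling unit is named, and a mixed model is also a parametric regression. The primary analysis accounts for families, and the stated aim is valid standard errors. If individual caregivers were resampled, the simulation suggests about 8.5% false positives against 5.5% with family resampling at ICC 0.15 (400 runs, so each figure is uncertain by one to one and a half points). That is a conditional risk. The 0.15 itself is for the parenting score, at a cluster level the text does not name.
- **That mediator and outcome are taken at the same interview.** The 10-week time point belongs to the primary analysis. The mediation text assigns no time points, the figures are not shown, and three assessments make an ordered model possible. Making the 3-month outcome the main model would be a choice of estimand, not the correction of an error.

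The last two are details that a condensed article commonly leaves to the full protocol or analysis plan.

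**Conclusion.** The concern holds for the significance condition, which is written in the text. It makes reporting of a stated secondary objective selective, and its scope across the four mediators is undefined.

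The harm is modest and depends on the unknown mediator effects. With 384 caregivers, ICC 0.15 and correlation 0.6 assumed for the mediators, the arm-to-mediator path is overstated about 1.3-fold, with no estimate in about 37% of trials, at 0.2 SD. At 0.3 SD the figures are 1.04-fold and 7%. If baseline adjustment gained nothing, they would be about 1.5-fold and 55%, and 1.14-fold and 22%. For mediator effects clearly above 0.3 SD the condition hardly matters.

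A reader might infer that the mediation analysis has inflated type I error, invalid standard errors or no time order. The first is contradicted by the check; the other two are not established by the document.

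**What to change.** In Evaluation of mediation, delete the significance condition. State that all four indirect effects will be estimated and reported with confidence intervals whatever the between-group p-values of the mediators.

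This is a change of wording and needs no new data. The cost is a few extra secondary estimates, some of which may be null or imprecise.

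To confirm at the same time, as clarification only: that the bootstrap resamples whole families, which are the randomised unit, and at which assessments mediator and outcome are taken.

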**Fig. 4 Fig4:**
[figure not shown]
Putative mediation of impact of CSI on parenting by caregiver stress, caregiver distress, caregiver psychosocial wellbeing, and stress management. Solid lines represent mediational pathways to be tested

Since all the measures are continuous, the indirect effects will be calculated by multiplying relevant pathways and bootstrapping will be used to produce valid standard errors for the indirect effects. All analyses will adjust for baseline measures of the mediators (Caregiver Stress Scale, caregiver distress (K10), stress management, outcome (Parenting scale) and putative measured confounders (e.g., socioeconomic status).

### Facilitators

Prospective CSI facilitators must meet the following criteria to be accepted into the 6-day training:
Native Arabic speakerPreferably from the geographic locations of implementationMinimum age 24 yearsHigh school education required, university education desirableAt least 2 years of experience implementing psychosocial interventions, preferably with adults, even more preferably with parents/caregiversEmotionally mature and receptive to the core ideas of the CSI regarding parental wellbeing and positive parenting, as assessed during an interview with the CSI lead trainer and supervisor and possibly other relevant WCH staffAble to commit to attend the full training, all sessions of the intervention, and all supervision meetingsRespectful and tolerant to different nationalities and religious groupsBeing a parent is highly desirable but not required
While we recognize the potential bias of being a parent (facilitators with children may bring in their own experiences and attitudes to the intervention), in our experience we have found that participants view facilitators with children as having greater legitimacy to lead sessions on parenting knowledge and skills; in addition, facilitator-parents may have a deeper appreciation for the challenges and stressors that parents face. We make every effort, in training, supervision, and on-site coaching, to ensure that any bias introduced to the sessions by facilitators, whether due to having children or any other source, is minimized.

### Facilitator training

CSI facilitators first participate in a 6-day training which combines didactic and experiential components, and includes extensive practice implementing the intervention within the training group. In addition to covering the specific content of the sessions (e.g., parental stress and wellbeing, relaxation exercises, coping with anger and frustration, child development, positive parenting), trainees also learn group facilitation skills through extensive role-playing and continuous feedback. The trainers complete a detailed competency checklist for each trainee at the start and completion of the training; trainees also complete a knowledge and attitudes assessment at the start and completion of the training. Only those trainees who are deemed sufficiently knowledgeable and skilled, based on a trainer-completed competency checklist and the pre-post knowledge assessment, are then invited to become CSI facilitators. During their first full implementation of the CSI, facilitators are observed a minimum of three times with the competency checklist completed on each occasion, and receive weekly supervision.

### Childcare during CSI sessions

Childcare will be provided on-site for up to two children per participant. Trained and experienced animators (child care providers) trained by War Child Holland in child care and child safety will care for children, with two animators available during each session. The childcare sessions are not structured, and no formal activities are facilitated, in order to avoid providing any index children attending the childcare with a substantive psychosocial experience that might confound the results of the study. Various play materials and snacks will be provided, and the child care workers will ensure the safety and comfort of all children.

### Intervention fidelity assessment, quality control, and supervision

A fidelity checklist will be completed jointly by the co-facilitators immediately after each session of the CSI. The number of items on the fidelity checklist varies by session, as it covers all of the activities specific to each session. The research implementation coordinator and the CSI trainer and supervisor will conduct three on-site observations in each group and provide coaching to all new facilitators based on these observations. They will use the fidelity checklist and a supplementary competency checklist to guide their feedback. They will also meet with all pairs of facilitators weekly for supervision. Registers will be used to record attendance at all sessions of all CSI groups. These will be kept in the secure care of the research implementation coordinator. The research implementation coordinator and CSI trainer and supervisor will receive their own supervision weekly from War Child Holland’s Lebanon-based psychosocial coordinator, and biweekly supervision from a psychologist and faculty member the University of Balamand ([name]).

The PI will hold weekly meetings with the research coordinator and research implementation coordinator to review all activities and issues and ensure fidelity to the research protocol.

### Minimization of contamination

To minimize contamination, randomization will be at the family rather than individual parent level, in order to avoid having parents/caregivers within the same family assigned to different arms of the study. To minimize contagion between the CSI and control arms, participants in CSI groups will be asked to avoid sharing program content, including the relaxation and stress management exercises, with anyone outside of their immediate household.

### Masking of outcome assessments

All assessments will be carried out by trained research assistants (see the “Research assistants” section for details about background and training of the research assistants). Efforts will be made to minimize interactions between the intervention and research teams during the study. As noted earlier, the rationale for keeping the RAs blind is explained to participants at each assessment, along with a request that they not reveal their group assignment. This was accomplished successfully during the pilot study, and we anticipate no difficulties replicating this in the present study.

### Nested qualitative study

Following the intervention and within 3 weeks after the post-intervention data collection, focus groups discussions will be conducted by the research coordinator and a trained research assistant with all groups of CSI participants (male and female separately), to examine perceptions of the intervention, perceived impact on personal wellbeing and parenting, and barriers to accessing the intervention and to utilizing intervention content. The focus groups will also explore participants’ experience of completing the assessment battery (e.g., level of difficulty, perceived burden).

### Data management

Participants will be assigned a study ID, and their names will not appear on any data collected. Questionnaire data will be uploaded directly by the research coordinator to the secure KOBO server, from which it will be downloaded to WCH’s own secure server and entered into SPSS (quantitative) or NVivo (qualitative). All data will be backed-up securely at the WCH Amsterdam office, and all data and analysis files will be securely password protected and encrypted. For all questionnaire data, range and consistency checks will be performed within days post data-entry, which will occur immediately following each wave of data collection. Any queries identified will be resolved promptly by the trial management team. A detailed WCH data management policy will serve as guidance on all data management issues. Focus group notes will be taken verbatim in Arabic, translated into English, and entered into NVivo, where they will be coded and analyzed by the research team.

### Trial management

A committee will monitor the progress of the trial. Trial monitoring will comprise the collation and reporting of routine trial process indicators and adverse events (AEs)*.* Summary statistics and graphs showing trends over time will be compiled for the process indicators. No interim analyses are planned. In addition to the PI ([name]), and [name], an international leader in the field of family and early childhood research, additional members of the trial management committee include [name], co-investigator on the project and director of Research and Development at War Child Holland, and [name], the research coordinator for this study.

### Risk mitigation

The CSI is a non-pharmacological, non-clinical intervention. Although the target population is in a high-adversity setting, there is minimal risk to participant safety or wellbeing from participation in this study. During three earlier cycles of implementation including the pilot RCT, while the intervention was being developed and finalized, there were no instances of serious AEs, or of any AEs related to the intervention or research methods. Referrals *were* made for social or medical assistance in eight cases (illness, eviction, and gender-based violence). All CSI facilitators as well as all research assistants are trained to identify signs of distress and to report any possible AEs to their supervisor. All facilitators receive weekly supervision, both to ensure fidelity and quality of implementation and to support their own skill development and wellbeing.

### Adverse events

We will monitor the occurrence of AEs using the War Child Holland (WCH) Adverse Events Reporting Procedure. A data safety and management committee (DSMC) will provide oversight on AEs and safety protocols for the study. The DSMC will be composed of individuals to be named prior to the start of the trial, none of whom will be a part of this study. The key terms of reference for the DSMC will be to review reports of AEs (within 48 h of notification). Reviews should occur on a 12-monthly basis via Skype. The purpose of the DSMC is to monitor the occurrence of AEs and where required make decisions on further actions to be taken to determine whether AEs are likely to be related or unrelated to the intervention. The DSMC will have the mandate to recommend stopping the study if it is determined that the risks of the study outweigh the benefits.

All AEs reported spontaneously by participants or observed by the investigators or other staff members will be recorded by the research team on WCH’s Adverse Event reporting form. AEs can be detected by anyone as all study staff will be trained in their detection and management. Intervention facilitators will initially discuss AEs reporting with their supervisor, who will report this to the research coordinator. Research assistants will initially discuss AE reporting with the research coordinator. The research coordinator will subsequently share all AEs with the PI, who will be responsible for ensuring appropriate responses to all AEs. All AEs will be reported to the DSMC. This will occur within 24 h for AEs. The chair or nominated person from the DSMC will review AEs within 48 h and the DSMC will review all AEs monthly and where necessary to determine whether AEs are likely to be related or unrelated to the intervention.

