### Intervention

The CSI is a nine-session weekly group intervention, co-facilitated by trained non-mental health professionals, who receive 6 days of training, three on-site observations with feedback, and weekly supervision. Groups are offered separately to women and men and are run with 10–12 participants. Table 1 lists session topics and corresponding modules, along with the stress management technique(s) taught in each session.

**Table 1 Tab1:** CSI sessions, modules, and stress management/relaxation methods

Session	Topic	Module
1	Introduction and group building *SM*: Participants’ own methods of coping with stress*	Caregiver wellbeing
2	Stress and relaxation *SM: Counting the breath*	Caregiver wellbeing
3	Lowering our stress *SM: Stepping back from our thoughts, grounding*	Caregiver wellbeing
4	Coping with frustration and anger *SM: Peaceful walking, various anger management techniques*	Caregiver wellbeing
5	Parental stress and influence *SM: Stepping back from our thoughts (repeat)*	Parenting in adversity
6	Increasing our influence as parents, part I: Positive attention *SM: Guided visualization: A safe place*	Parenting in adversity
7	Increasing our influence as parents, part 2: Effective discipline *SM: Informal breathing practice*	Parenting in adversity
8	Positive parenting: Practice *SM: Participants choose any stress management/relaxation method*	Parenting in adversity
9	Looking back, looking forward	Closure

*SM* stress management/relaxation technique taught during the session

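### Adverse events are recorded when volunteered or noticed, and CSI caregivers have far more staff contact than waitlist caregivers, so any count by arm would lean towards more events in CSI

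*Protocol article*

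**What the plan says.** The Adverse events section says what is captured: "All AEs reported spontaneously by participants or observed by the investigators or other staff members will be recorded by the research team". It adds that "AEs can be detected by anyone as all study staff will be trained in their detection and management". Risk mitigation names two groups of reporters: "All CSI facilitators as well as all research assistants are trained to identify signs of distress and to report any possible AEs to their supervisor". Facilitators have their own channel: "Intervention facilitators will initially discuss AEs reporting with their supervisor, who will report this to the research coordinator".

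The contact schedule comes from other sections:

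- Intervention: "The CSI is a nine-session weekly group intervention, co-facilitated by trained non-mental health professionals".
- Baseline, post-intervention, and follow-up assessments: "Questionnaire data will be gathered at three time points: baseline, post-intervention, and 3-month follow-up". Two of these three fall after randomization, and both arms have them.
- Control group: waitlist families are offered the CSI only once the 3-month follow-up is done.
- Retention of participants: each arm has its own social event in each wave.
- Nested qualitative study: focus groups are held with CSI participants only.

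Table 2 lists no adverse-event item among the questionnaires. The safety committee is asked to judge whether events are related to the intervention, and it may recommend stopping the study if risks outweigh benefits.

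**The concern.** Under a passive rule, an event enters the record only if a caregiver mentions it to staff or staff notice it. Facilitators are trained reporters, and until the 3-month follow-up they meet CSI caregivers only. The same illness, eviction or episode of violence therefore has more chances of being recorded in a CSI family than in a waitlist family.

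Background events do occur in this population: Risk mitigation reports eight earlier referrals for problems of this kind. To decide whether an event is plausibly due to the programme, or whether risks outweigh benefits, the committee would want to know how often such events happen without the programme. The waitlist arm is the natural source of that rate, and as described it is observed less completely. A harmless programme could appear to carry an excess, while events in waitlist families go unrecorded.

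**Working it through.** The article gives no adverse-event rate, arm comparison or detection probability, so there is no stated figure to reproduce. The check counts contacts from the text and then shows what they imply over a range of assumed detection chances.

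**Step 1. Scheduled face-to-face contacts per caregiver, randomization to 3-month follow-up**

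| Contact | CSI | Waitlist |
|---|---|---|
| Sessions | 9 | 0 |
| Post-intervention and 3-month assessments | 2 | 2 |
| Subtotal | 11 | 2 |
| Social event | 1 | 1 |
| Focus group | 1 | 0 |
| Total | 13 | 3 |

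The contact ratios are 11/2 = 5.5 and 13/3 = 4.3. A caregiver attending seven sessions, the protocol's threshold for completion, gives (7 + 2)/2 = 4.5.

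**Step 2. Chance that an event is recorded**

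Let p be the chance that one contact brings an event to light (assumed, equal in both arms) and k the number of contacts. Then

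P(recorded) = 1 − (1 − p)^k.

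With equal true risk, the expected ratio of recorded events, CSI to waitlist, is [1 − (1 − p)^k_CSI] / [1 − (1 − p)^k_WL]. For example, at p = 0.10 with 11 against 2 contacts:

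(1 − 0.9^11) / (1 − 0.9^2) = 0.686 / 0.190 = 3.6.

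| Assumed p | Ratio, 11 against 2 | Ratio, 13 against 3 |
|---|---|---|
| 0.02 | 5.0 | 3.9 |
| 0.05 | 4.4 | 3.4 |
| 0.10 | 3.6 | 2.7 |
| 0.20 | 2.5 | 1.9 |
| 0.30 | 1.9 | 1.5 |
| 0.50 | 1.3 | 1.1 |

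**Step 3. The same in counts**

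Take 240 caregivers per arm (Randomization and blinding), an assumed true risk of 10% in both arms, and p = 0.10. Each arm then has 240 × 0.10 = 24 true events.

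- 11 against 2: 24 × 0.686 = 16.5 recorded in CSI, 24 × 0.190 = 4.6 in waitlist.
- 13 against 3: 24 × 0.746 = 17.9 in CSI, 24 × 0.271 = 6.5 in waitlist.

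**Step 4. What the model leaves out**

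It gives every event the full set of contacts. An event arising after the last session has no session left in which to surface, so for such events the arms differ at most by the focus group. Contacts are also not equally revealing: one assessment can bring out anything since the previous one. Both points pull the true ratio towards 1. The direction does not change, because CSI caregivers have every type of contact that waitlist caregivers have, plus more.

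**Step 5. Effect of asking everyone the same question**

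If only answers to an identical question at the two shared assessments are compared, the expected ratio under equal risk is 1.0. If session reports are pooled with those answers, and the question has sensitivity s per visit, the ratio is [1 − (1 − s)^2 (1 − p)^9] / [1 − (1 − s)^2]. For assumed s of 0.7 to 0.9 and p of 0.05 to 0.20 this lies between about 1.00 and 1.09.

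**The case against.** Several objections have force.

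- **No planned comparison.** A reader might infer that a planned adverse-event analysis is biased. The Data analysis section contains no between-arm test of adverse events, Trial management rules out interim analyses, and the committee reviews events case by case. Judging a single event does not require an arm ratio. This stands: the point reaches only a tabulation by arm and the committee's sense of background frequency.
- **Unseen procedure.** A reader might infer that events are captured in no other way. The section refers to War Child Holland's reporting procedure, which is not shown and may include structured questioning. This also stands, so the point concerns the rule as the article describes it.
- **Unknown size.** The only related figure is eight referrals over three cycles. The pilot alone had 151 caregivers, so that is at most 8/151 = 5.3% per caregiver. Referrals are not adverse-event counts, but nothing here supports a confident estimate of a large excess.
- **Safety can still be judged.** A reader might infer that neither safety nor harm could be concluded. That goes too far. Distress, stress, wellbeing and harsh parenting are measured in both arms at every assessment by blinded assessors, and worsening on these is a main plausible harm of a psychosocial programme. Events caused by the programme can arise only where it is delivered, which is where detection is strongest. A low CSI count would still reassure.
- **Equal assessor contact.** Research assistants see both arms alike. This narrows the gap, but the sessions and the facilitator channel remain on one side.

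Together these reduce the point without removing it. The article states the capture rule expressly, and nothing in it balances detection between the arms.

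**Conclusion.** The point holds as a minor one. As described, capture depends on contact with staff, and contact is 11 against 2 occasions, or 13 against 3, in favour of CSI. Under equal true risk, a count by arm would be expected to show more events in CSI, which works against the intervention. The direction follows from the documents, given equal detection per contact. The size does not: the ratios of 5.0 to 1.3 and 3.9 to 1.1 rest on assumed detection chances of 2% to 50%, full attendance, and events open to detection at every contact. What is weakened is the waitlist background rate available to the safety committee and to any descriptive safety table. The primary outcome and the stated efficacy analyses are untouched.

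**What to change.** First check whether War Child Holland's procedure already asks all caregivers about adverse events in the same way. If it does, one sentence in the protocol saying so settles the matter.

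If not:

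1. Add one neutrally worded adverse-event question to the tablet questionnaire for every caregiver in both arms, at the post-intervention and 3-month assessments.
2. Place it after all outcome items, so that an answer revealing the arm cannot affect the ratings from that visit.
3. Base any between-arm adverse-event summary on those answers only.
4. List events detected at CSI sessions separately.
5. Leave spontaneous reporting and the existing route to the safety committee as they are.

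No visit is added. The costs are more background events to process and a small added risk that a caregiver reveals the allocation to a blinded assessor, which could carry over if the same assessor sees that caregiver again.
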